##### Safety

Falls during the intervention period could be a possible risk or complication. The incidence of falls during the intervention period as main safety outcome will be documented in the physical activity diary. Additionally, falls within the last 6 months before the start of the intervention will be assessed.

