### Recruitment

Every potential study participant, patients, GPs and additionally in the intervention group PTs and home care nurses, will receive written and verbal study information and will be required to give written informed consent. The identification and recruitment of clusters (GP practice and their patients), PTs and home care nurses are presented (see Fig. 1).

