**Fig. 1 Fig1:**
[figure not shown]
Recruitment and flow of all participants

In a first step, GP practices will be identified by searching GP registers in each study region. Cooperation networks will be consulted and the project will be presented to professional associations. Included GPs will then select potential patients as participants by searching their data bases for relevant ICD Codes (see Table 1) within the past 3 years. The GP will send a study invitation letter to eligible patients. Interested patients will make an appointment for the informed consent discussion with the GP. If included patients in the intervention group receive home care, their home care nursing services will be informed about the study. The director of the home care service will be asked to select at least two nurses, who are in contact with the participating patient at least than once a week, to attend the educational training (see Implementation strategies). PT practices will be identified through asking included GPs for existing cooperation and through regional searches. Identified PT practices will receive an invitation letter. If interested, the head of the PT practice can select up to two PTs to attend the educational training.

**Table 1 Tab1:** ICD Codes for having recent or chronic complaints of VDB

ICD codes	Explanation
F45.8	Other somatoform disorders
G43.1	Migraine with aura
G62	Other and unspecified polyneuropathies
G63	Polyneuropathy in diseases classified elsewhere
H81	Disorders of vestibular function
I95.1	Orthostatic hypotension
R26 (without R26.1)	Abnormalities of gait and mobility
R29.6	Repeated falls
R42	Dizziness and giddiness

As incentives, participating GP practices receive a case payment per patient (60 €). Participating PT practices will receive a case payment per patient (30 €), and home care services will receive a training on the ‘National Expert Standard in Long Term Care on mobility’ [33] after the study.

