#### Control group

To avoid performance bias, we aim to keep GPs and patients masked regarding group allocation. Therefore, we provide an active control intervention for the control group cluster (GPs and their patients). It consists of a 30-min online educational training on the German national guideline ‘acute dizziness’ for GPs [17], which is held by a GP.

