**Table 2 Tab2:**
[figure not shown]

[figure not shown]
Schedule of enrolment, interventions, research outcomes and assessments according to SPIRIT

*GP* general practitioner, *PT* physiotherapy, *VDB* vertigo, dizziness and balance disorders

In the intervention group, GPs and if requested their medical assistants will participate in a two hours lasting educational training. The training will be held by a VDB expert and neuro-otologist and will include an update on recent diagnostic and therapeutic developments for VDB in older patients, as well as an introduction into the use of the checklist for diagnostic screening. The PTs will receive a 1-day educational training called ‘Dizziness and/or balance disorders in the vestibular rehabilitation of older patients in primary care’ which enables the participating PTs to understand the procedure according to the decision tree and enables them to apply it. To make sure, that the PTs can transfer their knowledge into practice, there will be the opportunity so share treatment videos and receive feedback from the expert. Both events will be held live online. After 8 weeks, GP practices and PTs will be invited to a 1-h online moderated follow-up workshop to exchange experiences about the study and ideas to improve the communication in an interdisciplinary team working in primary care. A pocket card for the home care nurses serves as a reminder on their role as supporters of the patients’ adherence to the intervention (reminders on potential physiotherapeutic exercises, making and keeping appointments, filling out the exercise diary, fall prevention measures). In addition, they will receive a training about VDB in older people, fall prevention and their role in the study. All participants will receive step-by-step instructions on the study process. Moreover, there will be a telephone hotline for all participant groups to answer their questions on content and methodology and to respond to problems or needs in a timely manner.

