#### Secondary outcome measures

##### Physical activity

The main secondary outcome is the qualitative and quantitative change in daily-life physical activity measured by wearable sensor-based actigraphs from movisens [38]. In addition, patients will be asked to fill in a physical activity diary about their activities of daily living and occurrence of VDB.

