## Discussion

Due to the experiences gained from our pilot study, we have critically and carefully revised our recruitment, intervention and implementation strategies. First, the recruitment options are expanded in terms of the use of various approaches (e.g. involvement of local networks, use of faxes, call for participation via website and newspaper). Medical assistants are incorporated in the whole study process, as they are the primary point of contact with the practice and relationships with practice staff are considered as essential for maintaining commitment to the study [51, 52]. The adherence to the intervention protocol by the GPs and PTs will be improved by using a revised version of the checklist and decision tree, revised educational trainings (e.g. more hands-on exercises), the provision of supportive materials and a study folder with all relevant study documents. Team work between different health professionals is considered as a key to deliver high quality primary care [53]. To establish interdisciplinary team working in primary care, communication is a main facilitator [54]. In order to stimulate the interdisciplinary exchange between GPs and PTs, we will perform a workshop after 8 weeks to share experiences and ideas. To improve the patients’ adherence and motivation even in the absence of informal caregivers, we involve home care services which receive a pocket card containing reminders on relevant study topics (e.g. filling physical activity diary). In addition, patients will be assisted by the study team in filling in the questionnaires and the physical activity diary. The physical activity diary and the corresponding manual were revised to make it more understandable and easier to be filled in for the target group. The assessment of physical activity behaviour by the International Physical Activity Questionnaire [55] and the use the actigraphy device StepWatch™ resulted in missing values or seemed not to be appropriate for our target population as reported in other studies [56, 57]; thus, it would not be used in the present study anymore.

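### Falls, the main safety outcome, are recorded in a patient-kept diary that only intervention-arm home care nurses are reminded about, so falls may be recorded more completely in that arm

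*Protocol article*

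**What the plan says.** The Safety section of the protocol article names the data source: "The incidence of falls during the intervention period as main safety outcome will be documented in the physical activity diary". The same section adds falls in the 6 months before the intervention. Under Physical activity the diary is described as patient-kept: "patients will be asked to fill in a physical activity diary about their activities of daily living and occurrence of VDB".

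The Discussion explains how diary-keeping is supported: "we involve home care services which receive a pocket card containing reminders on relevant study topics (e.g. filling physical activity diary". The Methods (Implementation strategies) list the card's contents as including "making and keeping appointments, filling out the exercise diary, fall prevention measures".

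The nurses belong to one arm. Recruitment says that consent is sought from patients and GPs and "additionally in the intervention group PTs and home care nurses", and later: "If included patients in the intervention group receive home care, their home care nursing services will be informed about the study". The Control group section describes only a training for GPs: "It consists of a 30-min online educational training on the German national guideline".

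The primary objective covers safety as well as effectiveness. The Discussion also says that the study team will help patients with the questionnaires and the diary, without distinguishing the arms.

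**The concern.** A recorded fall is the product of two things: that it happened, and that someone wrote it down. A between-arm comparison of recorded falls is interpretable when the second is the same in both arms. Here a reminder that acts on the recording exists in one arm only. The nurses are chosen for regular, roughly weekly contact with the patient, so the reminder can recur through the 4-month intervention period.

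If the reminder works, more falls are written down in the intervention arm at the same true rate. An apparent excess could then be wholly or partly ascertainment. The same nurses are also trained in fall prevention, so a true reduction could be offset by fuller recording, and the diary alone cannot separate the two. The comparison at risk is the one offered for the safety part of the main objective.

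**Working it through.** The plan states no figure on this point, so there is none to reproduce. The check has two parts.

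**1. The text, side by side**

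| Question | Intervention arm | Control arm | Section |
|---|---|---|---|
| Where are falls in the intervention period recorded? | Physical activity diary | Same | Safety |
| Who fills it in? | Patient | Patient | Physical activity |
| Do home care nurses take part? | Yes, if the patient has home care | No | Recruitment; Control group |
| Is there a diary reminder through nurses? | Yes, on the pocket card | None described | Discussion |
| Does the study team help with the diary? | Yes | Yes (no arm named) | Discussion |

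The arms differ in the nurse rows only. The Harms section adds the hotline, notes on checklists and decision trees, and patient interviews. None of these is tied to a count of falls, and checklists and decision trees are tools of the intervention, so they do not restore balance.

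**2. How large could the effect be?**

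All inputs are assumptions; the article gives none of them.

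- h: share of patients with home care, 10% to 40%
- r: fall rate in home care patients relative to the others, 1 or 2
- c0: share of falls recorded without the nurse reminder, 0.60 to 0.80
- c1: share recorded with it, 0.90

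Share of falls that occur in home care patients: s = h·r / (h·r + 1 − h).

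Recorded-falls ratio, intervention to control, with no true difference: [(1 − s)·c0 + s·c1] / c0 = 1 + s·(c1/c0 − 1).

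- Low: h = 0.10, r = 1, so s = 0.10; c0 = 0.80. Ratio = 1 + 0.10 × (0.90/0.80 − 1) = 1 + 0.10 × 0.125 = 1.01.
- Middle: h = 0.20, r = 2, so s = 0.40/(0.40 + 0.80) = 0.333; c0 = 0.70. Ratio = 1 + 0.333 × 0.286 = 1.10.
- High: h = 0.40, r = 2, so s = 0.80/(0.80 + 0.60) = 0.571; c0 = 0.60. Ratio = 1 + 0.571 × 0.50 = 1.29.

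A second set with equal fall rates (r = 1, so s = h) and c1 = 0.90:

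| c0 | h = 10% | h = 30% | h = 50% |
|---|---|---|---|
| 0.80 | 1.01 | 1.04 | 1.06 |
| 0.70 | 1.03 | 1.09 | 1.14 |
| 0.50 | 1.08 | 1.24 | 1.40 |

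The 1.40 needs half the patients in home care and half of unprompted falls missed.

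Study-team help acts by raising c0 towards c1. If it raised c0 from 0.70 to 0.80 in the middle case, the ratio would fall to 1 + 0.333 × 0.125 = 1.04. If it raised c0 to 0.90, the ratio would be 1.00.

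Masking is the same arithmetic reversed. If the intervention lowered the fall rate evenly in all its patients, a distortion of 1.10 would make a true ratio of 1/1.10 = 0.91 look like no difference.

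**The case against.** The strongest case on the other side has five parts.

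- **The diary may not be the only source.** A reader might infer that falls in follow-up are recorded nowhere else. The article does not establish that. Secondary objectives lists falls as an outcome separately from safety in terms of falls, Outcomes places secondary outcomes at baseline, 4 and 6 months, and Table 2, which gives the assessments, is not shown. A falls question at those visits may already exist. This stands, and the fix is conditional on it. It does not alter that the main safety outcome, as worded, is the diary count.
- **Few patients may be affected.** The nurse reminder reaches only intervention patients with home care, and all patients are community-dwelling and able to stand up on their own. With 120 patients allocated 1:1, that is 60 per arm, so 10% and 20% in home care would be 6 and 12 patients. This stands as a limit on size. Against it, the Abstract describes the card as also being for informal caregivers, so its reach could be wider.
- **Diary support is otherwise general.** Study-team help is offered without distinction by arm, and the diary and its manual were revised for easier completion. This may narrow the gap; nothing stated says it closes it.
- **The Methods wording is weak support.** There the card mentions "filling out the exercise diary, fall prevention measures", in a list that starts with physiotherapy exercises. The exercise diary may be a different document. If so, the link rests on the single example in the Discussion, which does name the physical activity diary.
- **Recall is no clean substitute.** Recall over 2 to 4 months in older patients, with Mini-Mental State scores down to 20 allowed, misses falls, and blinding of assessors does not make the patient's recall equal in both arms. This stands, and is why a falls question should support the diary and not replace it.

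**Conclusion.** The concern holds as a built-in risk of unequal ascertainment: a diary reminder exists in one arm only, and it acts on the record from which the main safety outcome is taken. The likely direction is a higher recorded count in the intervention arm, among patients reached by the card.

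A reader might go further and conclude that falls are counted more completely in one arm, or that the safety comparison is biased by design. The documents do not support that. They give no diary completeness by arm, no home care share and no evidence that the reminder works, and they describe help with the diary that is not limited to one arm.

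The range of about 1.01 to 1.29 is an illustration and no estimate. It rests wholly on the assumed home care share, capture rates and relative fall rate, and runs from negligible to material. The point deserves correction because the remedy is cheap and falls that were never written down cannot be recovered by analysis.

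**What to change.** 1. Keep the diary as the prospective record of falls, and make prompting the same in both arms: give the same diary reminder directly to all patients, or take that line off the nurses' card.
2. If Table 2 does not already provide it, have the blinded research assistants ask the same structured falls question in both arms at 4 and 6 months, in the form of the baseline item. The 4-month visit closes the intervention period. Label this a supporting measure.
3. Report diary completeness by arm.
4. Add a sensitivity analysis of falls restricted to patients without home care at baseline. This also serves patients already followed. It needs baseline home care status recorded alike in both arms, and it does not remove any prompting through informal caregivers.
5. Use one name for the diary in Implementation strategies and in the Discussion, or state that there are two.

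The cost is a small change of materials in a running trial, so early and late clusters may differ slightly in prompting and the date of the change should be recorded. Beyond that it takes one question at visits already planned and two simple analyses. Recall at 4 and 6 months will miss some falls, which is acceptable in a supporting measure.

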##### Falls efficacy scale—international version

We will examine concerns to falls during physical activities and the social dimension of fear of falling using the German version of the Falls Efficacy Scale—International Version, which consists of 16 items [39]. The German version has a high internal and test-retest reliability [40].

##### Mini-balance evaluation systems test

We will investigate static and dynamic balance by using the validated German Version of the Mini-Balance Evaluation Systems Test [41]. It has four domains: anticipatory proactive balance, reactive postural control, sensory orientation and dynamic gait and 14 items.

##### European quality of life five-dimension five-level scale

The health-related quality of life will be assessed by the German version of the European Quality of Life Five-Dimension Five-Level Scale (EQ-5D-5L). The five dimensions are mobility, self-care, usual activities, pain/discomfort and anxiety/depression. The validity and reliability are assessed as sufficient to be used in economic evaluation studies [42].

##### Health-related resource use in an elderly population

Healthcare resource utilisation and medication will be assessed using the validated ‘Questionnaire for Health-Related Resource Use in an Elderly Population’ (Fragebogen zur Inanspruchnahme medizinischer und nicht-medizinischer Versorgungsleistungen im Alter). It consists of 14 items and is a valid tool to determine health related resource use in older population [43].

#### Additional data sources

To describe the sample and potential confounder, additional data will be assessed: Sociodemographic information (age, gender, family status) for descriptive purposes, the Barthel Index [44, 45] to assess the independence in basic daily activities, the Mini Mental Status Test [31, 46] to measure cognitive impairment and the Questionnaire of Chronic Illness Care in Primary Care [47] to assess structural and personal characteristics from GP practices and an adapted version for PT practices and home care nursing services.

### Process evaluation

To not only assess whether a complex intervention is effective but to understand how and under which circumstances the intervention is working, a process evaluation is an essential part of testing complex interventions [48]. Therefore, we will monitor the whole study process with a process evaluation, which is based on our logic model (see Additional file 1).

The process evaluation follows the Medical Research Council guidance for complex interventions [28] along with an adapted version of Grant’s framework for designing process evaluations of cluster-randomised trials [49]. We aim to shed light on essential aspects of the process, including the recruitment and reach of participants, the delivery of the intervention to and response of all participants including implementation. In addition, mechanisms of impact and context will be examined [48]. To thoroughly monitor the expected behaviour change (see Additional file 1), as well as the other factors mentioned above, we will use a mixed-methods approach (Table 3). Individual interviews will be conducted at *t*_2_ with all GPs and with the half of PT practices and group interviews with 20% of the home care nursing services. We will also conduct interviews with about 15 patients of the intervention group and 15 of the control group at timepoint *t*_0_ and *t*_2_. The interviews of t_0_ will focus on the treatment of VDB before the study and the attitude towards the intervention.

**Table 3 Tab3:** Schedule of process evaluation according to SPIRIT

	Study period				
	Enrolment	Data collection point			Close-out
**Timepoint**	***-t***_***1***_	***t***_***0***_	***t***_***1***_	***t***_***2***_	***Post t***_***2***_
**Treatment pre study**					
Interviews with patients		X			
**Recruitment and reach**					
Contact protocol	X				
Cancellation forms	X				
Individual interviews with all participants		X		X	
**Delivery**					
Standardised evaluation forms for the educational trainings including supportive materials	X				
Implementation protocol	X				
Field notes via checklist/decision tree				X	
Field notes of contact via telephone or email		X	X	X	
Interviews with all participants				X	X
**Response**					
Field notes of contact via telephone or email		X	X	X	
Field notes via checklist/decision tree				X	
Interviews with all participants				X	X
Evaluation of the telephone helplines					X
**Unintended consequences**					
Field notes of contact via telephone or email		X	X	X	
Field notes via checklist/decision tree				X	
Interviews with all participants					X
**Context**					
Interviews with all participants				X	
**Data collection procedures and organisational aspects**					
Field notes by the study assistant afterwards each measurement appointment		X	X	X	
Interviews with all participants					X

### Health economic evaluation

The objective of the health economic evaluation is to estimate the cost-effectiveness of the intervention in terms of additional costs per additional patient who experienced a decrease of 12 points on the DHI questionnaire between *t*_0_ and *t*_2_. Moreover, a cost-utility analysis will consider the additional costs per additional quality-adjusted life year (QALY).

The health economic evaluation will be performed from a societal perspective. Therefore medical and non-medical resource utilisation will be measured for retrospective periods of 6 months at baseline and at *t*_2_ using the Health-Related Resource Use in an Elderly Population. For monetary valuation of resource utilisation, unit costs will be calculated for all services and goods (privately purchased or prescribed) in Euro.

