#### Secondary objectives

Secondary outcomes are physical activity, static and dynamic balance, falls and fear of falling as well as quality of life. We will also evaluate the safety in terms of falls. Cost-effectiveness and cost-utility of the CPW will be assessed in a health economic evaluation alongside the trial. To understand the behaviour change process, as well as barriers and facilitating aspects of implementation, the study will be accompanied by a comprehensive process evaluation.

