### Eligibility criteria

#### Patients

Primary target population are community-dwelling older patients aged at least 60 years, who consulted their GP with recent or chronic complaints of VDB. They should be able to stand up on their own and stand for two minutes with support.

Exclusion criteria for patients are:Not able to give written informed consent,A DHI less than 12 points [30]. A DHI of at least 12 points is required, since the suggested minimal clinical important difference is 12 points [30] and patients with a lower DHI score are not at risk to reach the effectiveness threshold.Moderate to severe cognitive impairments as defined by the Mini-Mental State Examination of less than 20 points [31],The presence of psychiatric disorders identified by International Statistical Classification of Diseases and Related Health Problems (ICD) codes (F10.-F19, F20.-F29, F30., F31., F32.2, F32.3, F32.8, F32.9, F33.2, F33.3, F33.8, F33.9),Limited life expectancy (≤ 1 year) due to an advanced disease with a poor prognosis estimated by GP,VDB caused by current substance abuse,Unable to complete questionnaires and follow instructions because of insufficient command of the German language.

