### Intervention

#### Experimental intervention

The intervention is an algorithmized evidence-based multidisciplinary CPW to enhance the care of older persons with VDB and thus promote their mobility and participation in daily living. It illustrates all steps of the patient pathway through a standardised approach consisting of two main components:A paper-based *checklist for standardise clinical decision making*, which contains evidence-based diagnostics, treatment and referral options for the whole treatment period and is applied by previously trained GP. The aim of the checklist is to help the GP to make a classifying diagnosis, to guide the next steps and to prioritise them.A *decision tree* for evidence-based physiotherapeutic clinical reasoning and treatment of VDB. It consists of recommendations and options for anamnesis (including information about clinical pattern), specific assessments, treatment and evaluation. The decision tree will be applied by previously trained PT, if the treating GP prescribes physiotherapy.

At the beginning of the 4-month intervention period, the patients make an appointment with their GP who performs the anamnesis and the examinations based on the checklist. The anamnesis involves questions regarding the quality, character, frequency and duration of VDB and accompanying symptoms. Then, further examinations like position manoeuvre and neurological tests will be undertaken by the GP. Depending on the results of the anamnesis and examinations, the checklist contains suggestions for further referral and treatment (see Fig. 2). Referral suggestions can be the referral to a neurologist, otorhinolaryngologist, internist/cardiologist and PT. Treatment options may include symptomatic bridging therapy with medication or general treatments such as medication adjustment. The treatment by and therefore the referral to a trained PT is recommended when the checklist/GP comes to the following conclusions: the patient suffers from benign paroxysmal positional vertigo, other factors requiring examination by another physician specialist can be excluded and/or has taken place before with no results.

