**Fig. 2 Fig2:**
[figure not shown]
Intervention flow

The trained PT will use the decision tree for clinical reasoning and planning and applying the treatment. According to the decision tree, the PT will use systematic recommendations and options for a physiotherapeutic anamnesis, which leads to specific hypotheses. Following the algorithm, the PT is then able to differentiate and choose the right physiotherapeutic assessment. Based on the results, the decision tree leads him/her to a specific hypothesis and corresponding evidence-based treatment options (the main focus is on vestibular rehabilitation) including educational material for the patient, like home exercise programs and flyers with information. Last step will include the evaluation and documentation of the chosen therapy.

At the follow-up-visits after 4 weeks and 3 months, the GP will use the checklist again. In case of worsening of symptoms or 8 weeks PT without improvement, a referral to a medical specialist is recommended. In the event of a slight improvement in symptoms, PT is recommended for a further 4 weeks. If there is significant improvement after 4 weeks, only the second follow-up examination is suggested. In the event of significant improvement after 3 months, the treatment is successfully completed within the context of the study. A modification of the intervention is not planned. There are no restrictions regarding concomitant treatments and interventions during the trial.

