### Outcomes

The primary and secondary outcome will be assessed on patient level in the intervention group and control group at three measurement points: at baseline before the intervention (*t*_0_), after 4 months (*t*_1_) and after 6 months (*t*_2_). Additional data on GP practices, PT practices and home care nursing services level will be assessed at *t*_0._ For an overview of the research outcomes and assessments, see Table 2.

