### Data analysis

The data analysis of the measured outcomes will be done by a blinded biostatistician who is not involved in the study. The primary analysis will be based on a linear mixed model of the DHI changes between t_0_ and t_2_, using intervention group and initial DHI as fixed factors and a random intercept for cluster. The statistical inference will be based on the Wald *t*-test for the intervention on an alpha level of 5% (two-sided). Similar models will be applied for exploratory analyses of the secondary outcomes. No pre-specified subgroup analyses are planned. Due to the restricted sample size, no additional adjustments for other fixed effects are planned. Range and cross-checks of the outcome variables and key baseline patient characteristics will be performed. Impossible or implausible data will trigger queries to the team of the principal investigator. All analyses will be based on the intention-to-treat principle. In case of dropouts, the last available observation will be carried forward. No interim analyses are planned.

For the process evaluation, quantitative data will be analysed descriptively. Qualitative data from interviews and field notes from research team, GPs and PTs will be analysed with content analysis [50], which will be performed by two independent researchers from the study centres.

To analyse the cost-effectiveness of the intervention, an incremental cost-effectiveness ratio and an incremental cost-utility ratio will be calculated as the ratio of the difference in mean cost and the difference in mean health effects (DHI or QALY) between study groups during the 6-month follow-up period. Non-parametric bootstrap method will be employed to generate confidence intervals around the difference in mean cost and the difference in mean health effects. Uncertainty surrounding the cost-effectiveness ratio and cost-utility ratio will be presented on the cost-effectiveness plane. Furthermore, cost-effectiveness acceptability curves, based on the incremental net-monetary benefit will be constructed. The study will be terminated when all collected data have been analysed and utilised within the analysis plan.

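### The protocol conflicts on whether resource use is collected at t1; without it, patients lost between t1 and t2 have no follow-up cost, and literal carry-forward would supply a pre-intervention one

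*Protocol article*

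**What the plan says.** Three places in the protocol article bear on when resource use is collected.

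- Health economic evaluation: "medical and non-medical resource utilisation will be measured for retrospective periods of 6 months at baseline and at" t2. This names two time points and one look-back length.
- Outcomes: "The primary and secondary outcome will be assessed on patient level in the intervention group and control group at three measurement points", namely baseline (t0), 4 months (t1) and 6 months (t2).
- The subsection on health-related resource use, which stands under Secondary outcome measures: "Healthcare resource utilisation and medication will be assessed using the validated" 14-item questionnaire for older people.

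The list in Secondary objectives points the other way on whether resource use is a secondary outcome at all: "Secondary outcomes are physical activity, static and dynamic balance, falls and fear of falling as well as quality of life". Resource use is absent from it.

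On the period of interest, the economic comparison is made "between study groups during the 6-month follow-up period", and the intervention occupies the first part of it: "At the beginning of the 4-month intervention period, the patients make an appointment with their GP". Further GP contacts follow: "At the follow-up-visits after 4 weeks and 3 months, the GP will use the checklist again".

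Data analysis applies intention-to-treat to all analyses, fills in dropouts by carrying forward their last value, and gives no separate rule for costs. The Sample size section allows for 23% dropout among 120 patients.

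**The concern.** A reader cannot tell from the text whether a cost form exists at t1. This matters because cost is the numerator of both the cost-effectiveness and the cost-utility ratio.

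If the two-point schedule is the real one, costs and effects are observed on different schedules. DHI and EQ-5D-5L are taken at t1, at the end of the 4-month intervention period; cost is not. A patient who leaves between t1 and t2 then contributes an effect observed after the intervention, but a cost observed only before it. The general carry-forward rule, applied as worded, would pair the two. In the pathway arm, that means an effect with none of the pathway's contacts costed against it.

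A lesser matter is recall. Under the two-point schedule, everything in the intervention period is reported from the older part of the t2 window, by patients aged 60 or over. The only cognitive exclusion is "Moderate to severe cognitive impairments as defined by the Mini-Mental State Examination of less than 20 points".

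**Working it through.** **1. The two schedules side by side (months from t0).** Under the economic section, forms at t0 and t2 cover months −6 to 0 and 0 to 6. For completers the second window matches the follow-up period exactly, so there is no gap.

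Under the Outcomes section, a form is also given at t1. If the stated 6-month look-back applied there too, the t1 form would cover months 4 − 6 = −2 to 4, and the t2 form months 0 to 6. The two would overlap in months 0–4, and summing them would count those months twice. So if the three-point reading is meant, the look-back in the economic section is incompletely described.

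**2. The plan's dropout figure.** Sample size section: (1.96 + 0.84)² × 2 × 25² × 1.36 / 12² = 92.56. Then 1 − 92.56/120 = 22.9%, which reproduces the stated 23%. In patients, 120 − 92.56 = 27.4, about 27 without a t2 form. The figure is used here only as the plan's own allowance for loss.

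**3. Patients with a t1 effect but no follow-up cost.** The split of losses before and after t1 is not given. Over an assumed range of the share lost after t1:

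| Share of losses after t1 | Patients affected | % of 120 |
|---|---|---|
| 0% | 0 | 0 |
| 25% | 6.9 | 5.7 |
| 50% | 13.7 | 11.4 |
| 75% | 20.6 | 17.2 |
| 100% | 27.4 | 22.9 |

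For each of these patients, a t1 form would retain 4/6 = 67% of the follow-up cost period, against 0% under the two-point schedule.

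**4. What literal carry-forward does.** For a patient lost after t1, the last DHI is from t1 and the last cost is from t0 (months −6 to 0). The effect is post-intervention and the cost pre-intervention. For a patient lost before t1, both values are from t0, so they are at least matched, although the cost is still not a follow-up cost. The mismatch between numerator and denominator therefore comes from losses between t1 and t2.

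**5. Recall lag (month of form minus month of contact).**

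| Contact | Lag at t2 | Lag at t1 |
|---|---|---|
| Intervention period, months 0–4 | 2–6 months (midpoint 4) | 0–4 months (midpoint 2) |
| 4-week visit (28/30.44 = 0.92 months) | 5.1 months | 3.1 months |
| 3-month visit | 3 months | 1 month |

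The documents give no data on completeness of recall, so this step yields lags and not a bias.

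**The case against.** The strongest reply is that the economic section is the specific rule for this instrument and the Outcomes sentence a general one. Secondary objectives omits resource use, so the conflict rests mainly on the heading under which the questionnaire is described. Table 2, to which the Outcomes section refers, is not shown and may resolve it. This stands in part: the two-point schedule may well be the intended one, and a reader should not conclude that t1 collection is definitely absent or definitely planned. But the text gives two answers and needs one. If the answer is two time points, the loss of follow-up cost after t1 is real.

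Second, handling of missing costs commonly belongs in the analysis plan, which is not shown. The absence of a cost-specific rule is therefore no finding. What remains is that the rule the article does state covers dropouts without exception and does not suit costs.

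Third, the 6-month look-back matches the follow-up period, the instrument is described as validated in older people, visits are in the patient's home, and the Discussion says the study team helps with the forms. All of this stands. The recall window is a design choice with a limitation, not an error.

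A reader might infer that poor recall understates the cost difference by a definite amount in the pathway's favour. The documents do not support that. Assuming that 70–90% of older contacts are reported and deriving a 10–30% shortfall merely restates the assumption. The direction depends on whether the pathway raises or lowers resource use. Control patients recall over the same window, and referrals or physiotherapy following the 3-month visit can fall in months 4–6, the best-recalled part. Nor do the documents support the inference that late t2 visits cut off the first weeks of care: no visit window or lateness is stated.

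**Conclusion.** The point holds as a conflict on timing with one concrete consequence. The Outcomes and resource-use subsections together imply collection at t0, t1 and t2; the economic section specifies baseline and t2 only. Under the latter, between 0 and about 27 of 120 patients would have an effect measured at t1 and no post-baseline cost. Carry-forward taken literally would give them a pre-intervention cost.

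The range assumes that dropout equals the planned 23%; its position within the range depends on when losses occur, which is not given. The effect on either ratio cannot be sized: it depends on that timing, on the split by arm and on how baseline costs compare with follow-up costs. The longer recall is a limitation of unknown size and direction. The primary DHI analysis is not touched, so the point is worth acting on but confined to the secondary economic evaluation.

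**What to change.** State one schedule in the Outcomes, resource-use and economic sections, consistent with Table 2. Preferably, give the resource-use form at t0 (look-back 6 months), at t1 (since t0) and at t2 (since t1), and sum the t1 and t2 amounts for the 6-month follow-up cost. State that baseline costs are not carried forward as follow-up costs, and that periods without a form are treated as missing by a method named in the analysis plan.

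The first cluster entered in December 2021, so some t1 visits may already have passed. For those patients, keep the 6-month look-back at t2, record which schedule applied, and treat follow-up cost as missing if t2 is not reached.

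The cost is one 14-item form at a home visit that already takes place, with slightly more patient burden. Follow-up windows of 4 and 2 months would no longer match the 6-month baseline window, and the questionnaire would be used with recall periods other than the 6 months now planned. If the sponsor prefers two time points, the minimum is to say so consistently and to exclude costs from the carry-forward rule.
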